#### Pre-pregnancy body mass index (BMI)

Pre-pregnancy BMI will be obtained from clinic records. BMI will be computed using Quetelet’s Index. World Health Organization (WHO) classification of BMI will be used for weight status classification [48]. BMI classification is divided into six categories based on WHO recommendations as depicted in Table 2.

**Table 2 Tab2:** BMI classification according to WHO guidelines [47]

Classification	BMI range (kg/m^2^)
Underweight	< 18.5
Normal	18.5–24.9
Overweight (Pre-obesity)	25.0–29.9
Obese class I	30.0–34.9
Obese class II	35.0–39.9
Obese class III	≥40

#### Outcomes measures

The main outcomes of this study are birth outcomes and infant outcomes which will be assessed at 6 and 12 months of age, respectively. The secondary outcomes include gestational weight gain (GWG) and infant feeding practices.

#### Gestational weight gain

Range of mean weight gain per week will be determined by deducting weight at assessment with pre-pregnancy maternal weight. Total GWG will be calculated as the differences between maternal weight measured at the last antenatal checkup (at or after 37 weeks period of amenorrhea) and pre-pregnancy weight recorded at the first antenatal appointment at the clinic (measured at < 12 weeks of amenorrhea) [49]. Weight gain recommendation for pregnancy will then be compared with the guidelines established by US Institute of Medicine (IOM). There are three classifications of GEG according to IOM guidelines which are inadequate, adequate and excessive. IOM guidelines on cutoff points for gestational weight gain are illustrated in Table 3.

**Table 3 Tab3:** Institute of Medicine (IOM) guidelines on gestational weight gain [12]

Pre-pregnancy BMI	Pregnancy weight gain goals (kg)
Underweight	12.5–18
Normal	11.5–16
Overweight	7–11.5
Obese	5–9

#### Birth outcomes

Birth outcomes such as birth weight, gestational age at birth, delivery method, duration of labor, instrument-assisted labor and other information about the experience during labor will be collected from clinic record. Data on low birth weight, preterm birth and intrauterine growth restriction (IUGR) will be identified through clinic records. Preterm birth is defined as a gestational age less than 37 weeks which may contribute to low birth weight with birth weight less than 2500 g [50]. IUGR refers to a condition in which the rate of fetal growth is below normal in light of the growth potential of a specific infant as per the race and gender of the fetus [51]. An infant with IUGR is defined as being below the 10% percentile of the recommended gender-specific birthweight for gestational age according to William’s curve [52, 53]. Focus on the birth outcome will be limited to the 3 major adverse birth outcomes: low birth weight, preterm birth, and intrauterine growth restriction (IUGR). These adverse birth outcomes are the leading causes of perinatal morbidity, mortality, neurodevelopmental impairments and disabilities among newborn babies [53].

#### CDC neonatal questionnaire

Neonatal questionnaire from Infant Feeding Practices Study (IFPS) II will be used to assess factors that affect infant feeding choices [54]. Questions on early feeding practices, including breastfeeding status, sources of information and sources of support are included in the questionnaire. These information are crucial as early feeding choices are crucial in influencing infant growth, especially in the first year of life.

#### Infant outcomes

##### Infant anthropometric assessment

Data on infant anthropometry will be assessed from infant book record at 6 and 12 months of age respectively. Anthropometry data of infants which comprises of head circumference, length and weight will be collected. Data will then be plot using WHO Growth Charts (include the reference, whereby weight for age, head circumference for age, length for age will be used).

##### Revised infant behavior questionnaire (IBQ-R)

Infant temperament refers to behavioral tendencies that is observed early in life and stable across age [55]. It is an important aspect that might contribute to infant physical growth [55]. Thus, infant temperament will be measured at 14–16 weeks using the validated RIBQ based on a 7-point Likert scale, from 1 (never) to 7 (always). Three major dimensions will be assessed: surgency/extraversion, negative affectivity and orienting/regulation. The IBQ-R has been validated for use for infants aged 3 to 12 months old [56] and its reliability has been reported in previous studies [57].

### Statistical analysis

All statistical analysis will be performed using SPSS software version 20 (SPSS Inc., Chicago, IL, USA). Continuous variables are presented as mean ± SD. Statistical probability level of *p* < 0.05 will be considered significant. Normality of continuous data will be tested using Q-Q Plot, histogram and Kolmogorov-Smirnov Test. Data of chronotype, sleep quality, depression, anxiety and stress, physical activity, BMI and GWG will be described in qualitative form. We will perform statistical analysis of the data quantitatively to examine the association between variables.

To determine circadian rhythm, we will perform circadian analysis of salivary melatonin and cortisol levels using Acrophase software. Circadian pattern of melatonin and cortisol secretion in 24-h will be represented in a graph. Circadian variables such as baseline (daytime melatonin level), acrophase (clock time at which the melatonin reaches peak level) and amplitude (difference between baseline and peak level) will be extracted from circadian analysis. Diurnal cortisol slope will be tabulated based on two data points (awakening and 21:00) by subtracting value at 21:00 from awakening value, and dividing by the number of hours between these two time points. Chronotype of respondents will be presented as categorical variables of Morning-type (M-type), Neither-type (N-type) and Evening-type (E-type). Student’s paired t-test will be used for comparing circadian variables during second and third trimester. Correlation between chronotypes and sleep quality will be assessed using Pearson’s correlation test.

We will perform regression to determine the association between circadian variables and depression, anxiety and stress scores and step count. Energy and nutrient intake as well as distribution among meals. Multivariable generalised linear models will be used to examine the associations between chrononutrition data (energy and nutrition intake as well as distribution between meals, duration between the last meal and sleeping time, meal frequency and eating window). We will also perform ANOVA to analyse the association between circadian variables with eating behaviors including breakfast-skipping, late-night eating and intermittent fasting.

To further examine the association between the circadian variables with total gestational weight gain, birth outcomes (birth weight, gestational age at birth), infant outcomes (weight, body composition and infant temperament scores), multiple linear regression will be used, with covariates such as maternal age and pre-pregnancy BMI. Odds ratios and 95% confidence intervals will be used to determine the strength and precision of each association after adjusting for potential confounders.

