## Background

Circadian rhythm is an endogenous process that has a periodicity of approximately 24 h [1]. It stimulates anticipation of regular and daily repeating events that take place at approximately the same time of day in organism, allowing the upregulation of most of the major physiological systems in mammals [2]. Circadian system in mammals is organized in a hierarchic manner in which the master (central) clock located in the suprachiasmatic nuclei (SCN) of the anterior hypothalamus govern this process [1, 3]. The SCN coordinates other central circadian oscillators including the hypothalamus and pituitary gland, which subsequently organizes the peripheral (local) clocks located in the peripheral tissues and aligns the entire circadian system to the external light/dark cycle [1, 3]. This allows organisms to coordinate endogenous and behavioral activities to the time of day, promoting internal and external synchronization.

Melatonin and cortisol are the most widely used biological phase markers to examine circadian rhythm [4, 5]. The secretions of these hormones are highly rhythmic, with melatonin exhibiting maximal level in the middle of night and gradual decline towards dawn while cortisol peaks in the second half of the night toward early morning, and declines to half of the peak value in the afternoon [6, 7]. Both melatonin and cortisol play a role in synchronizing the circadian rhythms in peripheral tissues to the 24-h pattern and likely provide feedback to the SCN [8].

Many emerging studies addressed the recognition of the importance of maternal circadian rhythm on pregnancy and fetal development. Throughout gestation, the fetus is inevitably exposed to maternal rhythms such as body temperature, food intake and melatonin level [9]. Entrained 24-h rhythms of fetal heart rate, movements and hormones were reported in human, non-human primates and sheep, suggesting that maternal circadian signals may contribute to the entrainment of the peripheral clock in fetus [9]. A study by Seron-ferre and his co-researchers proposed that fetal SCN and fetal organs are peripheral maternal circadian oscillators, which are entrained by maternal signals [9]. This results in internal temporal order during fetal growth, which subsequently allows for postnatal integration of the scattered fetal peripheral circadian clocks into an adult-like circadian system [9].

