##### Salivary melatonin and cortisol rhythm

In the present study, melatonin and cortisol will be measured using saliva samples. Both melatonin and cortisol can be measured in saliva in their free form [7]. Salivary concentrations have been shown to give an accurate indication of free or biologically active melatonin and cortisol as compared to human serum [5, 18]. Measuring salivary melatonin and cortisol can be used to characterize production patterns over each 24-h study period to facilitate comparisons between individual. Moreover, saliva is preferable to serum as a non-invasive alternative to determine melatonin and cortisol level. The taking of blood can cause variation in salivary cortisol level due to the effect of stress [7, 19].

Passive drool method will be used whereby subjects need to tilt their head forward and drooled through a funnel into a centrifuge tube [20]. Saliva sample collection will be taken at 2 time points during pregnancy, at second and third trimester respectively. The first sampling process will start at awakening in all cases, followed by 9:00, 15:00, 21:00 and 03:00 taken at 6 hourly intervals over the 24-h period. This will be done by subjects themselves and each subject will receive individual education regarding the collection process prior to the start of the data collection. To avoid saliva sample contamination with food, subjects are advised to refrain from eating a major meal or brushing their teeth with toothpaste within 30 min of sample collection [21, 22]. No chocolate or bananas, alcohol, caffeine, nicotine or drinks with artificial colorants should have been taken within the prior 12 h and on the day of sampling [21–23].

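### Melatonin acrophase is a clock time, but the paired t-test, regression and ANOVA planned for it fix no time origin, so any pair crossing midnight would carry a 24 h error

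*Protocol article*

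**What the plan says.** All of this is in the protocol article.

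- **Variables (Statistical analysis).** The list reads "Circadian variables such as baseline (daytime melatonin level), acrophase" and then amplitude. The definition given is "acrophase (clock time at which the melatonin reaches peak level".
- **Tests on them (Statistical analysis).** A "paired t-test will be used for comparing circadian variables during second and third trimester", with no exception for acrophase. The same section plans regression of circadian variables with depression, anxiety and stress scores and step count, ANOVA with eating behaviours, and multiple linear regression with gestational weight gain, birth and infant outcomes. Continuous variables are summarised as mean ± SD. No time origin, wrapped difference or circular method is named.
- **When the peak is expected (Background).** The text describes "melatonin exhibiting maximal level in the middle of night and gradual decline towards dawn".
- **When saliva is taken (Salivary melatonin and cortisol rhythm).** After a sample at awakening, sampling is "followed by 9:00, 15:00, 21:00 and 03:00 taken at 6 hourly intervals over the 24-h period". The two night samples therefore lie on either side of midnight.
- **Chronotype (Statistical analysis).** "Chronotype of respondents will be presented as categorical variables of Morning-type (M-type), Neither-type (N-type) and Evening-type (E-type"). Shortly afterwards: "Correlation between chronotypes and sleep quality will be assessed using Pearson"'s test.

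**The concern.** Clock time is circular, whereas a t-test, a mean ± SD and a linear regression treat it as a straight line. On a 0–24 h scale, a woman whose peak moves from 23:30 to 00:30 is scored 0.5 − 23.5 = −23 h instead of +1 h, and the average of those two times is (23.5 + 0.5)/2 = 12.0, which is noon. In a regression or ANOVA the same two values look 23 h apart.

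Acrophase is the study's direct measure of melatonin timing. A few crossings could dominate the comparison between trimesters, and the same values feed the models relating circadian variables to lifestyle and to pregnancy and infant outcomes.

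**Working it through.** **1. The sample in which acrophase is measured.** Subsample size calculation gives effect size 0.82, type I error 0.05, power 0.95 and a total of 80. Read as a two-sided two-sample t-test (the article does not name the test), the noncentral t distribution gives power 0.947 at 39 per group and 0.952 at 40 per group, so 2 × 40 = 80. The figure reproduces, and 80/(1 − 0.2) = 100 reproduces the inflated size. I use n = 80 pairs below.

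**2. Effect of a few crossings.** Assumption: true paired differences have SD 1.5 h (the article gives none). Let k of n pairs cross midnight in the same direction, each with an error of 24 h, unrelated to the true difference.

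- Shift in mean = 24k/n
- SD = √[1.5² + 24² × (k/n) × (1 − k/n)]
- Standard error = SD/√80

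| k | Shift in mean | SD | Standard error |
|---|---|---|---|
| 0 | 0 | 1.50 h | 0.17 h |
| 1 | 24/80 = 0.30 h | √(2.25 + 576 × 0.0125 × 0.9875) = 3.06 h | 0.34 h |
| 2 | 48/80 = 0.60 h | √(2.25 + 576 × 0.025 × 0.975) = 4.04 h | 0.45 h |

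The shift runs against the true movement: a crossing to a later time adds −24 h.

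**3. Simulation of the paired t-test.** Assumptions: between-woman SD 1.5 h, within-woman SD 0.75 h, true delay +0.5 h, n = 80, 3,000 runs, and mean peak varied because the article gives no clock time.

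| Mean peak | Pairs straddling midnight | Mean estimate, raw times | Runs with p < 0.05, raw times | Mean estimate, wrapped differences | Runs with p < 0.05, wrapped or noon origin |
|---|---|---|---|---|---|
| 00 h | 22.5% | −2.31 h | 51% | +0.50 h | 98% |
| 01 h | 17.1% | −1.68 h | 36% | +0.50 h | 99% |
| 02 h | 9.0% | −0.67 h | 11% | +0.50 h | 99% |
| 03 h | 3.3% | +0.06 h | 13% | +0.50 h | 99% |
| 04 h | 0.8% | +0.38 h | 57% | +0.50 h | 98% |

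The 51% at a midnight peak is not useful power. The simulated SD of raw differences there is 10.49 h, so the typical t is −2.31/(10.49/√80) = −1.97, and significance is mostly in the wrong direction.

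Sensitivity at a 03 h mean peak: between-woman SD 1.0 h gives +0.37 h and 53% rejection; SD 2.0 h gives −0.20 h and 6%.

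With no true shift, raw times reject in 2.6% to 5.2% of runs, so false positives are not inflated. Crossings in the two directions then balance on average.

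**4. Chronotype and sleep quality.** Assumptions: n = 365 (Sample size calculation, before inflation), true r = −0.2, MEQ mean 52 and SD 9, PSQI mean 6 and SD 2.7.

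| Variables correlated | Mean r | Power |
|---|---|---|
| MEQ score and PSQI score | −0.196 | 96% |
| Three ordered chronotypes and PSQI score | −0.169 | 90% |
| Three ordered chronotypes and PSQI above 5 | −0.135 | 75% |

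Ordered categories shrink r by 1 − 0.169/0.196 = 14%. The sign stays correct, and type I error with three categories and the PSQI score is 3.7%.

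**The case against.** The strongest reply is that the test is sound and only a coding detail is missing. The remedy keeps the same paired t-test. The article does not prescribe 0–24 h arithmetic, and a condensed protocol commonly leaves time origins to an analysis plan. The planned Q-Q plots and histograms would show a difference of about 24 h. The article never says that values cross midnight, and the trimester comparison is not among the main outcomes.

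Much of this stands. A reader might infer that the paired t-test is the wrong test; the documents do not support that, since it suits baseline, amplitude and cortisol slope, and suits acrophase once recoded. A reader might also infer that the article itself puts values on both sides of 24:00. It does not: a peak in the middle of the night and samples at 21:00 and 03:00 make this plausible, no more.

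The reply is not complete, however. The article names both the variable, as a clock time, and the test, and that pairing taken literally is wrong for every pair that crosses midnight. Diagnostic plots may reveal this, but the repair would then be chosen after seeing the data, and a rank test on raw differences would still give crossed pairs the wrong sign. Acrophase also enters the outcome regressions, so the matter reaches beyond the trimester comparison.

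A reader might further infer that Pearson's test is invalid for chronotype. The text does not support this. The Statistical analysis section separates qualitative description from quantitative analysis of associations, numeric MEQ and PSQI scores exist, and ordered categories would attenuate the correlation without making it meaningless. What remains is loose wording.

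**Conclusion.** The point holds for acrophase only, and conditionally: it bites if raw clock times are analysed and some peaks fall either side of midnight. One crossing among 80 pairs then moves the mean by 0.30 h and about doubles the SD, from an assumed 1.5 h to 3.1 h. Under the simulated assumptions a true +0.5 h delay is estimated anywhere from −2.31 to +0.38 h, and rejection rates fall from 98–99% to 11–57%. The harm is a diluted or reversed estimate and lost power, not false positives. All these sizes rest on assumed mean peaks, SDs and shift, because the article gives none. It is worth correcting before analysis because the correction is free. The chronotype correlation needs only a clarification.

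**What to change.** Add one rule to the Statistical analysis section: before any mean ± SD, paired t-test, ANOVA or regression, acrophase is expressed as hours after a fixed daytime origin (for example 12:00, so that 23:30 becomes 11.5 and 00:30 becomes 12.5). For the paired comparison alone, differences wrapped to ±12 h serve equally well. Keep the paired t-test, and leave baseline, amplitude and cortisol slope as they are.

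As a separate clarification, state that the chronotype–sleep quality correlation uses the MEQ score and the PSQI global score.

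The cost is two sentences and one recoding step, with no new data and no change in sample size.

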## Discussion

Pregnancy is a critical period when the system and organs of a new human body develops. Any disruption to the environment in which the fetus grows may result in developmental adaptations that produce permanent alterations to structural and physiological metabolic functions of the fetus [58, 59]. A hypothesis proposed in 1990 by the British epidemiologist David Barker, known as the Barker hypothesis, states that the environment during embryonic and fetal development increases the susceptibility of developing certain postnatal diseases later in life [60]. These effects are referred to as fetal programming which highlights the potential link between maternal factors on fetal growth and subsequently, infant health.

Pregnancy is considered as a period susceptible to chronodisruption as pregnant women often undergo physical, physiological, social and emotional changes, which may alter their usual lifestyle. Sleep problems such as insomnia and sleep deficiency are among the common issues reported during pregnancy due to various factors such as endocrine changes, backache, increase in size, fetal movement, frequent urination, leg cramps, abdominal discomfort, heartburn and vomiting [61, 62]. Sleep/wake cycles are closely intertwined with the circadian system, and disrupted sleep during pregnancy could potentially affect maternal circadian rhythm [5]. Furthermore, due to the lifestyle modernization and common use of artificial lightning, problem of disrupted or irregular circadian rhythm is not limited to shift worker, but may pose a significant health risk on the general public as well.

The strengths of the study include the utilisation of objective and subjective measurement to determine individual aspects of circadian rhythm, namely Morningness-Eveningness questionnaire and salivary melatonin and cortisol rhythms. Measurement of melatonin and cortisol levels at specific time points across the day allows the characterization of the full 24-h rhythm, which gives a whole picture of circadian rhythm. The use of pedometer to measure physical activity could minimize under and over-reporting of physical activity which are common when reported using self-assessment questionnaires. Other than using infant weight and body measurements to assess infant outcomes, this study also looks at infant temperament, which is an important aspect that might contribute to infant physical growth. Data on infant feeding practices will be included as early nutrition plays a crucial role in influencing infant growth.

In term of limitations, multiple assessments during second and third trimester of pregnancy could reduce compliance and elevate maternal stress which in turn can result in increased drop-out rates. However, this could be minimized through frequent and positive interactions to encourage continued participation, such as knowledge sharing session with the subjects at the clinic. Another limitations of study is the lack of control for compliance to the protocol of saliva sampling, e.g. by an electric device. However, several steps are undertaken to ensure compliance, including individual education prior to sampling, use of use-friendly sampling kit with easily understood instructions and appointment will be planned to collect the samples from subjects’ house, which ease the samples returning process. Besides, this study will include parent report of infant temperament and feeding practices which may cause response bias.

Maternal circadian rhythm and its influence on pregnancy and birth outcomes in human studies are scarce. Majority of the past studies on circadian rhythm focuses on shift work and related abnormalities. Hence, there is a need to explore circadian rhythm among the general pregnant women. Data from this study will contribute to the gap in knowledge related to the role of circadian rhythm during pregnancy on birth outcome and infant growth in the first year of life. This study is expected to demonstrate an association between circadian rhythm with total gestational weight gain, birth and infant outcomes. The findings from this study can be used to develop evidence-based recommendations on improving maternal circadian rhythm during pregnancy. By identifying the role circadian rhythm has to play during pregnancy, it could contribute to the development of relevant intervention strategies as well as strengthening existing strategies and policies related to maternal and infant health in Malaysia.

